#### Further Analyses

Secondary outcomes (ie, global functioning, general anxiety symptoms, depressive symptoms, quality of life, self-esteem, and guardians’ rating of their child’s social anxiety) will be analyzed using Linear Mixed Effects Model as described earlier. In further analyses, therapy expectancy, therapy motivation (both adolescents’ and guardians’), and satisfaction with the intervention will be added as moderators. Categorical outcomes (eg, diagnostic status) will be analyzed using General Linear Mixed Effect Models with intervention condition, diagnostic status, and time course as fixed effects and participants as random effect. Additionally, Growth Mixture Modeling will be used to identify subpopulations with comparable growth trajectories of social anxiety and secondary outcomes over time (latent classes) and to identify predictors of these classes.

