**Methods:**

A total of 222 adolescents aged 11-17 years with subclinical social anxiety (N=166) or with a diagnosis of social anxiety disorder (N=56) are randomly assigned to the online intervention or a care-as-usual control group. The 8-week guided online intervention is based on the Cognitive Model of Social Phobia and evidence-based online interventions for social anxiety adapted to the specific needs of adolescents. The care-as-usual group will be given access to the online intervention after the follow-up assessment. Participants are assessed at baseline, at 4 and 8 weeks post intervention, and at 3-month follow-up assessment on the primary outcome, that is, social anxiety, on secondary outcomes (eg, level of functioning, fear and avoidance, general anxiety, depression, quality of life, self-esteem, and negative effects of the intervention), on potential moderators (eg, therapy motivation, therapy expectancy, and satisfaction with the intervention), and potential mediators (eg, therapeutic alliance and adherence to the intervention). Data will be analyzed based on an intention-to-treat approach and both groups (intervention and care-as-usual) will be compared at each assessment time point. Furthermore, potential mechanisms of change and generalization of intervention effects on daily life are assessed using an ecological momentary assessment procedure that includes items on maintaining mechanisms of social anxiety, social context, and affect. Participants are prompted 3 times a day during the first 8 weeks of the study and again for 2 weeks following the follow-up assessment.

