## Methods

### Study Design

This randomized controlled trial (RCT) investigates the efficacy of the online intervention SOPHIE for adolescents with subclinical social anxiety or a diagnosis of SAD. SOPHIE is compared to a CAU control condition in a 2×2×4 design with a 2-level between-subjects factor (2 experimental conditions: SOPHIE vs CAU), a 2-level between-subjects factor (2 diagnostic conditions: SAD vs subclinical social anxiety), and a 4-level within-subjects factor (repeated measures: baseline, midintervention at week 4, post intervention at week 8, and follow-up 5 months after randomization, ie, 3-months follow-up). All participants are additionally assessed in EMA surveys during the first 8 weeks (from baseline to postassessment) and for 2 weeks after follow-up assessment. Participants in the intervention group have additional process assessments at weeks 2 and 6 during the intervention.

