#### Guardian Assessment

Guardians who provide their email addresses on the consent form voluntarily are assessed at baseline, midintervention, postintervention, and follow-up. In all assessments, they rate their child’s social anxiety using the *Parents’ Questionnaire on Social Anxieties in Childhood and Adolescence* (German: Elternfragebogen zu sozialen Ängsten im Kindes und Jugendalter) [96]. In 18 items, statements about the adolescent’s behaviors and fears are rated on a 4-point Likert scale from not at all (0) to very much (3). Furthermore, guardians provide demographic data and answer questions about their child’s treatment motivation and expectations during the baseline assessment. The *Motivation for Youth's Treatment Scale* [86] assesses guardians’ motivation for treatment with 8 items rated on a 5-point Likert scale from do not agree at all (–2) to agree completely (2). The *Credibility or Expectancy Questionnaire—Parent Version* [97] measures guardians’ expectations of the online intervention using 6 items. In total, 4 items are rated on a scale from not at all (1) to very (9), and 2 items on a scale from 0 to 100%.

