#### Main Analyses

The primary outcome, that is, change in social anxiety, will be tested using Linear Mixed Effects Models. Time (baseline, midintervention, post intervention, and follow-up), intervention condition (SOPHIE and CAU), diagnostic status (SAD and subclinical social anxiety), and interactions (time*intervention condition; time*diagnostic status; intervention condition*diagnostic status; time*intervention condition*diagnostic status) will be specified as fixed effects, baseline SPIN value will be added as a fixed covariate and participant as a random effect to allow for between-person variation.

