#### Sample Size

The sample size of 222 was determined in 2 a priori power analyses for the primary research question using G*Power [106] based on an intention-to-treat approach to account for possible dropouts and repeated measures ANOVA. In the SAD group, we expected a small to moderate effect size (Cohen *d*=0.35) [18,107], and for the group with subclinical anxiety, a small effect size (Cohen *d*=0.20) [38,108-110]. For both groups, we assumed an α level of 5%, power of 80%, and a correlation between measurements of *r*=0.4. Consequently, the SAD group should consist of 56 participants, and the subclinical social anxiety group of 166 participants.

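### Read literally, the secondary-outcome models adjust only for baseline SPIN and use each scale's own baseline only as an unconstrained response row, which is valid but inefficient

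*Protocol article*

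**What the plan says.** Main Analyses (Protocol article) sets out one linear mixed model for SPIN. Its factors begin with "Time (baseline, midintervention, post intervention, and follow-up), intervention condition (SOPHIE and CAU", followed by diagnostic status, and its interactions are "time*intervention condition; time*diagnostic status; intervention condition*diagnostic status; time*intervention condition*diagnostic status". It adds that "baseline SPIN value will be added as a fixed covariate and participant as a random effect". Baseline is therefore one of the modelled time points, and SPIN is the only baseline score named as a covariate.

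Further Analyses then states that the secondary outcomes (functioning, anxiety, depression, quality of life, self-esteem and the guardian rating) "will be analyzed using Linear Mixed Effects Model as described earlier". It names no other covariate.

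Each of these scales has its own baseline. Table 1 ticks baseline for the adolescent measures, and Guardian Assessment says that guardians "are assessed at baseline, midintervention, postintervention, and follow-up". The abstract adds that "both groups (intervention and care-as-usual) will be compared at each assessment time point".

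**The concern.** For the primary outcome, baseline SPIN is the outcome's own baseline. For a secondary outcome it is a different scale, and its range is cut by the entry threshold of 16. A scale's own baseline is usually the strongest single predictor of its later values. Here it is collected but not used as a covariate.

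The introduction states hypotheses for several of these outcomes at post assessment and follow-up, so precision matters. Two readings of the treatment effect are affected:

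- **Time by condition.** A covariate that is constant within a person cancels from a within-person contrast. What remains is a difference in raw change.
- **Group difference at a single visit.** With SPIN as the only adjustment, chance imbalance in the scale's own baseline passes into the estimate.

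**Working it through.** **Inputs.** From Sample Size: "α level of 5%, power of 80%, and a correlation between measurements of *r*=0.4", d=0.35 (SAD) and d=0.20 (subclinical), and 56 + 166 = 222 participants. From Procedures: 1:1 allocation. From Study Design: four measurements. Assumed: r and d carry over to the secondary scales, complete data, equal variances, no difference between diagnostic strata, two-sided 5%.

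**1. The plan's own figure.** Repeated measures ANOVA, within-between interaction, with f=d/2, λ=N·m·f²/(1−r), df1=m−1 and df2=(N−2)(m−1):

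- SAD: f=0.175, m=4, N=56. λ=56×4×0.030625/0.6=11.43, df 3 and 162, power 0.810.
- Subclinical: f=0.10, m=4, N=166. λ=166×4×0.01/0.6=11.07, df 3 and 492, power 0.803.

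These are the smallest even N that reach 80%, so 56 and 166 are reproduced exactly. Two or three measurements, or a between-group test, do not give them. The powered test is therefore time by condition. No power is stated for any secondary outcome.

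**2. Time by condition as written.** With unit variance and correlation r, a change from baseline has variance 2(1−r)=2×0.6=1.20. With own-baseline adjustment of the later score, the variance is 1−r²=1−0.16=0.84, which is 30% less. With SE=√(4v/222):

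| Analysis | v | SE | Power, d=0.35 | Power, d=0.20 |
|---|---|---|---|---|
| Change contrast (as written) | 1.20 | 0.147 | 66% | 27% |
| Own-baseline adjustment | 0.84 | 0.123 | 81% | 37% |

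The ratio of the two variances is (1+r)/2. The reduction is therefore 35% at r=0.3, 25% at r=0.5 and 15% at r=0.7.

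**3. Which part of the change produces the gain.** Simulation of the week-8 effect (150 data sets, N=222, r=0.4, d=0.35, complete data, diagnosis omitted; SPIN correlation assumed 0.4 with the scale's baseline and 0.2 with later visits):

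- Four visits, SPIN covariate, time by condition: empirical SE 0.154, power 61%.
- Four visits, own baseline as covariate, time by condition: identical, SE 0.154, power 61%.
- Post-baseline visits only, own baseline as covariate: SE 0.122, power 77%.

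The levels differ from the closed form within simulation error. The pattern is the same: swapping the covariate alone does nothing for time by condition. In a separate simulation with 25% assumed dropout, the swap moved the average model SE only from 0.156 to 0.153.

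**4. Single-visit comparison.** If baseline SPIN correlates c with the later secondary score, SPIN-only adjustment gives v=1−c². The article gives no c, so a range is shown for d=0.35:

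- c=0: v=1.00, power 74%.
- c=0.2: v=0.96, power 76%.
- c=0.3: v=0.91, power 78%.

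Against 81% with the own baseline, the loss is about 3 to 7 points.

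**5. Where the illustration does not fit.** Guardians take part voluntarily, so N=222 is too large for the guardian rating. Table 1 shows no week-4 assessment of global functioning, so four visits do not apply to it.

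**The case against.** A reader might infer that the secondary scales' own baselines are ignored. The article does not support that: baseline is a level of time, so each scale's own baseline is a response row, and time by condition measures change from it. Nor is there bias, because SPIN is a legitimate prognostic covariate and randomisation protects the comparison.

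A reader might also blame the choice of SPIN for the whole step from 66% to 81%. That does not stand either. The step comes from taking baseline out of the response while adjusting for it, and the primary model has the same baseline row. SPIN alone accounts only for the single-visit loss. The main support for such comparisons is one general sentence in the abstract, which does not say how they are adjusted.

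It can further be said that the back-reference may mean only the same type of model, with the covariate understood to change, and that a condensed article may leave such detail to an analysis plan. The first part is possible. But the article does not leave the covariate open: it names one and carries the model over by reference. A reader following the text would fit SPIN, so the wording is worth settling.

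The borrowed inputs are a fair limit. r and d were set for the primary question, each d belongs to one diagnostic group and not to the pooled 222, and no power is promised for secondary outcomes.

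**Conclusion.** The point holds as a matter of efficiency. As written, the secondary models are valid, but they estimate treatment effects less precisely than the collected data allow. Under the assumptions above, the variance of the time-by-condition contrast is 1.20 against 0.84, and illustrative power is 66% against 81% (d=0.35) or 27% against 37% (d=0.20). The cause is mainly the unconstrained baseline row. The SPIN covariate by itself costs about 3 to 7 points at d=0.35, in single-visit comparisons only, and that range rests on assumed correlations. The figures show the scale of the effect and do not forecast power for any named secondary outcome. The improvement is worth making because it is nearly free.

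**What to change.** In Further Analyses, replace the back-reference with wording such as: *Each secondary outcome will be analysed in a linear mixed model with its post-baseline visits as the repeated response and its own baseline value as covariate (optionally by visit). Condition, diagnostic status, time and their interactions are fixed effects, and participant is a random effect.* Baseline SPIN may stay as an additional covariate. The treatment effect is then the adjusted group difference at post assessment and at follow-up. For global functioning the response has two visits, post assessment and follow-up.

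Make both changes together. Replacing SPIN by the own baseline while keeping baseline as a response row gains nothing for time by condition and uses the baseline twice. If the primary model is itself changed to drop the baseline row, the secondary wording must be changed separately; otherwise the back-reference would leave those models with no own-baseline information.

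The cost is one sentence before unblinding and one extra coefficient per model (or one per visit). No new data, visits or participants are needed.

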The primary objective of this study is to examine the efficacy of an online intervention called SOPHIE for adolescents with subclinical social anxiety or SAD compared to a care-as-usual (CAU) control group. Thereby, the name SOPHIE is derived from the German term “SOziale PHobIE” (social phobia). It is hypothesized that SOPHIE will be superior to CAU in reducing social anxiety symptoms post assessment and that the intervention effect will be maintained until follow-up assessment 3 months after intervention completion. Furthermore, it is hypothesized that SOPHIE will also have beneficial effects on secondary outcomes, such as depressive as well as general anxiety symptoms, level of functioning, self-esteem, and quality of life at post assessment and follow-up. It is further hypothesized that intervention effects will be moderated by therapeutic alliance, adherence, treatment motivation, and treatment expectation of the online intervention. Moreover, by measuring social anxiety symptoms in their natural context longitudinally, we will examine if intervention effects translate into everyday life and if the postulated maintaining factors of SAD function as mediators of change. Additionally, we intend to model the network structure of social anxiety symptoms at each time point and observe differences in networks of adolescents (eg, regarding age, gender, and severity of social anxiety).

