	Self-esteem	The *Rosenberg Self-Esteem Scale* [84] assesses self-esteem in 10 items on a Guttman scale. This questionnaire is applicable to different age groups; in this study, the adolescent version is applied.	✓		✓		✓	✓
	Therapy expectancy	The *Credibility or Expectancy Questionnaire* [85] assesses treatment expectancy and credibility with 6 items. There are 2 rating scales, 1 from *not at all* (1) to *very* (9) and another from 0 to 100%. For this study, the wording of the items was adapted to the target group of adolescents.	✓					
	Therapy motivation	The *Motivation for Youth’s Treatment Scale* (MYTS) [86] measures adolescent’s motivation for therapy through a self-report questionnaire. Eight items are rated on a 5-point Likert scale from strongly disagree (1) to strongly agree (5). All adolescents complete this assessment at baseline, only adolescents randomized to the intervention group complete the MYTS at week 2, 4, 6, and 8.	✓	(✓)^b^	(✓)	(✓)	(✓)	
	Negative effects of intervention	The *Inventory for assessment of negative effects in psychotherapy* (German: Inventar zur Erfassung Negativer Effekte in der Psychotherapy, Kinder-INEP; [87,88]) has been adjusted to the online format of the intervention, reducing the questionnaire by 6 items to 15 items. This questionnaire is only answered by adolescents in the intervention group.					(✓)	
	Satisfaction with the intervention	The *ZUF-8* is an 8-item questionnaire for global, unidimensional assessment of patient satisfaction [89]. The questionnaire was adapted accordingly to measure satisfaction with the online intervention. Adolescents randomized to the intervention answer questions on a 4-point Likert scale from 1 to 4.					(✓)	
	Therapeutic alliance	The *Working Alliance Inventory for guided Internet Interventions* (WAI-I; [90]) is a self-report questionnaire that measures therapeutic alliance in online interventions with therapeutic support. The 12 items rated on a 5-point Likert scale from *rarely* (1) to *always* (5) were adapted to adolescents. Only adolescents in the intervention group are assessed with the WAI-I.		✓	✓	✓	✓	

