	Adherence to the online intervention	Adherence is operationalized through the extent to which the online intervention is used. The number of finished modules, the number of completed exercises, and the time spent in the online intervention are recorded automatically. As in other studies of online interventions, adherence is calculated with respect to each of these variables and with respect to a composite measure [91].					(✓)	

^a^SAD: social anxiety disorder.

^b^Indicated time points in parentheses reflect assessments only administered in the intervention group.

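### Satisfaction is planned as a moderator of the SOPHIE effect but is measured only in SOPHIE, at week 8; alliance and adherence are moderators in the hypothesis and mediators in the plan

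*Protocol article*

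**What the plan says.** **Satisfaction.** Further Analyses states that the secondary outcomes "will be analyzed using Linear Mixed Effects Model as described earlier". The model referred to, under Main Analyses, contains time, intervention condition (SOPHIE, CAU), diagnostic status and their interactions. The next sentence lists therapy expectancy and therapy motivation, "and satisfaction with the intervention will be added as moderators". The Abstract gives satisfaction the same role. In Table 1 the entry for the satisfaction scale reads "Adolescents randomized to the intervention answer questions on a 4-point Likert scale from 1 to 4". Its single tick, at week 8, is in parentheses, and the table footnote explains: "Indicated time points in parentheses reflect assessments only administered in the intervention group".

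**Alliance and adherence.** The last paragraph of the Introduction says: "It is further hypothesized that intervention effects will be moderated by therapeutic alliance, adherence, treatment motivation, and treatment expectation of the online intervention". The Abstract instead names "potential mediators (eg, therapeutic alliance and adherence to the intervention", and Mediation Analyses assigns both to a 1-1-1 multilevel mediation model. On alliance, Table 1 says "Only adolescents in the intervention group are assessed with the WAI-I", with assessments at weeks 2, 4, 6 and 8. On adherence it says "Adherence is operationalized through the extent to which the online intervention is used", with a parenthesised tick at week 8. Under Procedures, CAU participants can open the programme only once their follow-up assessments and interview are complete.

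**Expectancy and motivation.** Table 1 schedules both for adolescents at baseline. Motivation is repeated at weeks 2, 4, 6 and 8 in the intervention group only.

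**The concern.** A moderator of SOPHIE versus CAU answers the question whether the difference between arms depends on a characteristic. Estimating this needs values of the characteristic in both arms. Interpreting it cleanly also needs the characteristic to be fixed before allocation. Satisfaction meets neither condition: CAU participants have no programme to rate, and SOPHIE participants rate it at the same assessment as the post-intervention outcome.

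The Discussion says that moderator analyses of intervention effects may show which subgroups of adolescents benefit most. A within-SOPHIE association presented under the label of moderation could be read as evidence of that kind, which it is not.

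For alliance and adherence the fault is different. Two of the four moderators named in the Introduction have no corresponding moderator test in the plan, and the same two variables carry another role elsewhere in the article.

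**Working it through.** **1. Number of participants.** The sample size of 222 can be reproduced. For the group-by-time interaction in a repeated-measures ANOVA, take f = d/2, k = 2 groups, m = 4 measurements, ρ = 0.4 and α = 0.05, with λ = f²·N·m/(1−ρ), df1 = (k−1)(m−1) = 3 and df2 = (N−k)(m−1).

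- SAD: f = 0.175, N = 56, λ = 0.030625 × 56 × 4 / 0.6 = 11.43, df2 = 162, power 0.810.
- Subclinical: f = 0.10, N = 166, λ = 0.01 × 166 × 4 / 0.6 = 11.07, df2 = 492, power 0.803.
- Total: 56 + 166 = 222. With 1:1 allocation (Procedures), 222 / 2 = 111 per arm, approximately.

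**2. Where each candidate moderator is observed (Table 1).**

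| Variable | SOPHIE | CAU | Role in the article |
|---|---|---|---|
| Expectancy (adolescent) | baseline | baseline | moderator |
| Motivation (adolescent) | baseline; weeks 2, 4, 6, 8 | baseline only | moderator |
| Satisfaction | week 8 | none | moderator (Abstract, Further Analyses) |
| Alliance | weeks 2, 4, 6, 8 | none | moderator (Introduction); mediator (Abstract, Mediation Analyses) |
| Adherence | recorded use, ticked at week 8 | none | as for alliance |

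**3. Can condition × moderator be estimated?** Take the columns intercept, condition, moderator M and condition × M, with 111 participants per arm.

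- *M measured in both arms at baseline:* the design has rank 4 of 4 on 222 participants. With all four time points and their interactions it is 16 of 16. The interaction is estimable.
- *M observed only in SOPHIE, complete cases:* condition equals 1 in every remaining row, so the condition column equals the intercept and condition × M equals M. The rank is 2 of 4 on 111 participants, or 8 of 16 with time. Neither condition nor condition × M is identified.
- *M set to 0 in CAU:* condition × M still equals M in every row. The rank is 3 of 4, so the interaction cannot be separated from the main effect of M.

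Diagnostic status and the baseline SPIN covariate were left out for simplicity. Adding them does not help, because condition remains constant wherever satisfaction is observed.

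**4. What remains estimable.** Within SOPHIE, time × satisfaction can be fitted. It describes how week-8 satisfaction goes together with change among those who received the programme. It contains no comparison with CAU.

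**5. Hypothesis against plan.** Of the four moderators in the Introduction, motivation and expectation are matched in Further Analyses. Alliance and adherence appear only under mediation.

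**The case against.** The strongest defence is that this is a condensed article. Further Analyses writes out no condition-by-satisfaction term and does not say that CAU participants enter the satisfaction model. A SOPHIE-only analysis may be intended, with details left to an analysis plan. It is true that the term is not written out. But the sentence follows directly on a model that contains both conditions, groups satisfaction with two true baseline moderators, and does not mark it as SOPHIE-only. If a within-SOPHIE analysis is meant, moderator is the wrong label, and no analysis plan can supply CAU values that are never collected.

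Several stronger readings are tempting but are not supported:

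- *That none of the planned moderator analyses can be run.* The problem is confined to satisfaction; expectancy and motivation can be tested.
- *That the plan discards every CAU participant, or would impute their satisfaction.* The loss follows from ordinary complete-case handling and is not stated. Multiple imputation is mentioned straight after a sentence on missing data in the Growth Mixture Models, and nothing says that it would be applied to satisfaction in CAU.
- *That moderator models for alliance and adherence fail in the same way.* No such models are written. For these two the fault is the conflict between sections.
- *That satisfaction merely reflects improvement.* This is plausible given the shared week-8 assessment, but the documents give no data on it.

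It is also fair to say that these are further analyses, not the primary one.

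**Conclusion.** The point holds in two parts. First, satisfaction cannot moderate the SOPHIE-versus-CAU effect with the data this trial collects: the interaction is not identified, and the only estimable version is a post-randomisation association in about 111 of 222 participants. Secondly, the article contradicts itself on alliance and adherence, and two of the four hypothesised moderators have no matching moderator test.

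The figure of 111 assumes that the full 222 are enrolled, that allocation is exactly 1:1 and that week-8 satisfaction is complete in SOPHIE; non-response would lower it. The identification result depends on none of these, only on satisfaction being absent in CAU.

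The primary SPIN analysis and the sample size are untouched. The correction should still be made, because moderators are part of the stated objective and of an explicit hypothesis.

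**What to change.** - **Abstract and Further Analyses:** limit moderators to baseline expectancy and baseline motivation, and test condition × time × baseline moderator. Say explicitly that the baseline motivation score is used, since the scores from weeks 2 to 8 exist only in SOPHIE. Guardian versions are available at baseline from participating guardians only, so those models will rest on a subset.
- **Satisfaction:** remove it as a moderator. Report it descriptively, or as a correlate of change within SOPHIE labelled as such.
- **Introduction:** remove alliance and adherence from the moderation hypothesis.
- **Abstract, Introduction and Mediation Analyses:** align them so that alliance and adherence are described throughout as SOPHIE-only process predictors. One workable example is week-4 alliance predicting later SPIN, adjusted for baseline and week-4 SPIN. Week-2 alliance could not be adjusted in this way, because Table 1 schedules SPIN at baseline, week 4, week 8 and follow-up but not at week 2.

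The change needs no new data, no added assessments and no change in sample size. The cost is rewording in four places and the loss of one moderator analysis that could not have been interpreted.
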